#### Missing Data

The proposed analysis allows for missing data values. We will use clinical judgment to explore possible mechanisms of missingness, and we will consider including multiple imputation in the primary analysis, irrespective of levels of missingness, assuming a missing not at random scenario is unlikely (although multiple imputation has been found to perform better than complete case analysis, in a simple missing not at random scenario as shown) [38].

#### Sample Size Calculations

##### DMW, Oviva, and Changing Health Evaluations

The primary outcome for participants and controls receiving usual care is the HbA_1c_ level after the intervention. With a ratio of 1:10 for participants to controls and assuming an SD of 15 mmol/mol in HbA_1c_ levels [39], a total of 86 participants and 430 controls provides 80% power to detect an HbA_1c_ level difference in means of 5 mmol/mol (5% significance level), which is considered the smallest clinically significant HbA_1c_ change. Assuming that 90% of participants provide data after the intervention, this requires a total of 96 participants.

Therefore, we aim to recruit at least 288 participants (96×3) to DMW from which recruitment to the 2 behavioral interventions (Oviva, n=96 and Changing Health, n=96) will occur.

If the required sample size for any intervention is not achieved, appropriate consideration will be given to the interpretation of the results in light of the large number of objectives and outcomes.

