#### Comparison Group

Within the short time frame available for the study, a randomized controlled trial will not be possible; therefore, the effectiveness of the interventions will be compared with groups of people choosing not to take up the offer of interventions. Data on this comparison group will be sourced from NHS Digital as part of the national GP Data for Planning and Research program. The comparison group will be sourced from patients registered in GM, the other inclusion and exclusion criteria being applied. Controls (not using the intervention) will be matched (up to 10:1) with study participants on age (+2 or −2 years), gender, ethnicity, and general practice. When appropriate, we will increase the number of controls per participant to enable additional matching on baseline levels of outcome measures, such as HbA_1c_ levels. Where there are clinically important differences between participants and controls in relation to other characteristics such as prevalent cardiovascular disease, we will include these variables as covariates regression models.

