##### MyCognition Evaluation

The primary outcome is the postintervention diabetes distress score (DDS). Assuming an SD of 0.92 for DDS [34], 89 patients and 445 controls (5% significance level) provide 80% power to detect a difference in mean DDS of 0.3. Assuming 90% of participants provide data after the intervention, this requires a total of 99 participants.

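### The HbA1c sample size states 1:10 participants to controls, but its 86 and 430, and the 96 and 288 derived from the 86, come from a 1:5 calculation

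*Protocol article*

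**What the plan says.** In the protocol article, under Sample Size Calculations for the DMW, Oviva and Changing Health evaluations, the calculation opens "With a ratio of 1:10 for participants to controls and assuming an SD of 15 mmol/mol" in HbA1c. It continues that "a total of 86 participants and 430 controls provides 80% power to detect an" HbA1c difference of 5 mmol/mol at the 5% level. It then allows for 90% of participants providing data afterwards, which gives 96, and multiplies by three to reach a DMW recruitment target of at least 288.

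Two other places bear on the ratio. The Comparison Group section says that controls "will be matched (up to 10:1) with study participants on age", gender, ethnicity and general practice. The MyCognition Evaluation section names no ratio but states that "89 patients and 445 controls (5% significance level) provide 80% power".

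**The concern.** The stated ratio and the stated group sizes contradict each other within one sentence: 430 controls for 86 participants is five each, not ten. The ratio is an input to the calculation, so either the wording is wrong or every number that follows is.

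This is the primary-outcome calculation for three evaluations. The protocol also says that interpretation will take account of whether the required sample size was reached for each intervention, and that needs one unambiguous required size. As written, someone checking whether enough matched controls were obtained could use 430 per evaluation (the stated number), 780 (the stated ratio at 80% power) or 860 (the stated ratio applied to 86 participants).

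**Working it through.** **Inputs.** From the HbA1c sample size paragraph: SD 15 mmol/mol, difference 5 mmol/mol, significance level 5%, power 80%, and 90% of participants providing data. The paragraph does not state sidedness. Two-sided is assumed, in line with the two-tailed test named in the Analysis section.

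**Ratio implied by the numbers.** 430/86 = 5.0.

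**Formula.** With k controls per participant, the normal approximation for the number of participants is

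n = (1 + 1/k) × (1.960 + 0.842)² × SD² / difference²

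Here (1.960 + 0.842)² = 7.85 and 15²/5² = 9.

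- k = 5: 1.2 × 7.85 × 9 = 84.8. The t-based calculation gives 85.09, rounded up to **86**, with 5 × 86 = **430** controls. This reproduces the plan's figures.
- k = 10: 1.1 × 7.85 × 9 = 77.7. The t-based calculation gives 77.88, rounded up to **78**, with 780 controls. This does not.

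**Could a one-sided test explain the gap?** No. One-sided 5% gives 67 participants at 1:5 and 62 at 1:10.

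**Power (two-sided, t-based unless noted).**

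| Participants | Controls | Ratio | Power |
|---|---|---|---|
| 86 | 430 | 1:5 | 80.4% |
| 78 | 780 | 1:10 | 80.1% |
| 86 | 860 | 1:10 | 83.8% |
| 43 | 430 | 1:10 | about 55% (normal approximation) |

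**Figures built on it.**

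- At 1:5: 86/0.9 = 95.6, rounded up to 96; 96 × 3 = 288. Both match the plan.
- At 1:10: 78/0.9 = 86.7, rounded up to 87; 87 × 3 = 261.

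**Cross-check with MyCognition** (SD 0.92, difference 0.3). 445/89 = 5.0. The t-based requirement at 1:5 is 88.90, rounded up to 89, with 445 controls, as stated. At 1:10 it would be 81.37, rounded up to 82, with 820 controls. Both sample size calculations were therefore run at 1:5.

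**The case against.** The strongest reply is that this is a slip of wording with no harmful consequence. Only the ratio is out of line: 86, 430, 96 and 288 all agree with one another, and 80% power is attached directly to 86 and 430. The matching plan sets ten as a ceiling, so powering on five while matching up to ten is coherent, and prudent where the match on practice, ethnicity and gender must be exact. Any error is on the safe side, because more controls raise power. Controls come from routine records on about 160,000 people. Enrolment had reached 316 by May 2021, already above 288.

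Most of this is right and limits the point. The Comparison Group and MyCognition sections are not themselves wrong. The first suggests where the 1:10 may have come from, and the second supports 1:5 as the ratio used. Total enrolment above 288 is reassuring for DMW, although it does not show that each behavioral intervention reached 96. None of this reconciles the sentence itself: the ratio it states does not produce the numbers it gives, and no other section resolves the difference.

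**Conclusion.** The concern holds. The stated 1:10 is inconsistent with 86 and 430, which reproduce at 1:5 and not at 1:10. The 96 and 288 inherit the 1:5 ratio. Taken at face value, the written ratio would need 8 fewer participants before loss (78 against 86), 9 fewer per group after loss (87 against 96) and 27 fewer overall (261 against 288), but 350 more controls per evaluation (780 against 430).

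The error costs no power. With 86 participants, power is 80.4% at five controls each and 83.8% at ten. These figures assume a two-sided 5% test and the plan's own simple comparison of two independent means, with no allowance for matching or clustering. The point should be corrected because it concerns the primary sample size, but it does not threaten the study's conclusions.

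**What to change.** In the HbA1c sample size paragraph, change the stated ratio from 1:10 to 1:5. The 86, 430, 96 and 288 then stand and use the same ratio as MyCognition's 89 and 445. It would help to state the 1:5 ratio in the MyCognition paragraph too, and to add a clause noting that the calculations assume five controls per participant while matching may supply up to ten. The cost is a one-sentence correction with no change to recruitment or analysis.

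If 1:10 is what was intended, the numbers must be restated. Keeping 86 participants means 860 controls and about 84% power, again without changing recruitment. Restating as 78 and 780 would lower the targets to 87 per group and 261 overall. That option is less attractive because it changes recruitment and relies on obtaining ten matches per participant, which the matching plan gives only as a maximum.

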##### MyCognition Evaluation

The primary outcome is the postintervention diabetes distress score (DDS). Assuming an SD of 0.92 for DDS [34], 89 patients and 445 controls (5% significance level) provide 80% power to detect a difference in mean DDS of 0.3. Assuming 90% of participants provide data after the intervention, this requires a total of 99 participants.

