**MyCognition-related objectives**
To assess average within-person changes in *diabetes distress scores*.To assess changes in cognition scores.To assess changes in referral rates for traditional psychological interventions (compared with controls and within-person changes).

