#### Inclusion and Exclusion Criteria for the Main Intervention (DMW)

The inclusion and exclusion criteria for the main intervention are presented in Textbox 2.

The goal will be to offer DMW to all 140,000 people with T2D in GM, and a clinician-facing version will be offered to all GM primary care staff. Behavioral interventions (Oviva or Changing Health) will be offered to a total of 600 patients each. MyCognition cognitive assessment will be offered to all DMW participants, and the intervention on cognitive function will be offered to the first 600 participants. Other digital interventions will be offered to DMW participants through the DMW interface as shown in Figure 1. Participants will be offered access to *additional digital interventions* through DMW.

Inclusion and exclusion criteria for the main intervention.

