#### Enrollment and Informed Consent

Enrollment to the DMW intervention will be facilitated through the website, and patients will be directed to the participant information sheet. Providing patients are aged ≥18 years and have a diagnosis of T2D, they will be able to express their interest in taking part in the study by submitting their contact details via the DMW website. Patients will register for web-based services via their general practitioner (GP) who will confirm their identity by checking their documentation. Patients are required to use these web-based service codes to register for DMW and answer a number of inclusion and exclusion criteria. Once registered (and where they match the criteria), the study consent form will be introduced. If and when completed and submitted, the patient’s account is activated, and they are enrolled in the study. When registered, but not matching the study criteria, the patient will be given access to DMW, but not entered into the study or consent process.

Enrollment to other digital interventions will also occur via the DMW website. On the basis of the inclusion and exclusion criteria, participants enrolled and using the DMW intervention will be invited to take part in additional substudies involving an additional digital intervention (Oviva or Changing Health allocated to alternate eligible participants or MyCognition). The above procedure for communicating participant information and obtaining informed consent will be repeated.

We will invite participants to enroll with either Oviva or Changing Health behavioral interventions until 600 have attended each intervention. These interventions will be offered to alternate participants enrolling with DMW, ensuring that the numbers receiving each intervention remain similar.

All DMW participants will be provided with the option of completing the MyCognition web-based cognitive assessment and will be offered the MyCognition intervention until 1000 have completed the intervention. When 1000 people have completed the intervention, DMW participants will continue to be offered the option of completing the MyCognition web-based cognitive assessment but will not be offered the MyCognition intervention. Participants will be invited to complete the MyCognition web-based cognitive assessment every 3 months during the study (a maximum of 3 times). Those completing these assessments, but without receiving the intervention, will act as a control group.

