#### MyCognition

To evaluate the MyCognition intervention, the University of Manchester will obtain participant and control data from MyCognition via DMW, from GP records via DMW, and from NHS Digital for the period April 1, 2016 to March 30, 2022. Participant data transferred to the university via DMW will include cognition scores, diabetes distress scores (administered as a web-based questionnaire to participants), and usability data.

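### The MyCognition power statement counts on 445 controls with a distress score, which the stated data sources and enrolment do not support

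*Protocol article*

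**What the plan says.** **Power.** Sample Size Calculations, MyCognition Evaluation, names the post-intervention DDS as the primary outcome. It begins "Assuming an SD of 0.92 for DDS" and concludes that "89 patients and 445 controls (5% significance level) provide 80% power to detect a difference in mean DDS of 0.3". Allowing for 10% loss, it asks for 99 participants. The control number is not inflated.

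**Source of the score.** The MyCognition data-items section lists, among participant data reaching the university via DMW, "diabetes distress scores (administered as a web-based questionnaire to participants". The NHS Digital item lists (under Diabetes My Way, and in the section on NHS Digital data for participants and non-consenting controls) contain no distress score.

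**Who the controls are.** Enrollment and Informed Consent invites DMW users to a cognitive assessment every 3 months, at most three times, and says: "Those completing these assessments, but without receiving the intervention, will act as a control group". Comparison Group describes comparators for all interventions as people who do not take up the offer, with data from NHS Digital.

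**The cap.** Enrollment and Informed Consent says that DMW users "will be offered the MyCognition intervention until 1000 have completed the intervention". The section on inclusion and exclusion criteria for DMW says that "the intervention on cognitive function will be offered to the first 600 participants".

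**The objective.** Textbox 1 words the distress objective as "To assess average within-person changes in" the score and names no control comparison, although it does so for referral rates. Design, Outcomes (Overview) and the sample size section all assume a comparison with controls, and Outcomes makes that comparison primary.

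**Enrolment.** The DMW aim is at least 288 participants, a figure built from the HbA1c calculation. Results reports 316 enrolled by 10 May 2021.

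**The concern.** For HbA1c, NHS Digital can supply many controls per participant because the outcome is in the GP record. The distress score is not described as being there. The MyCognition calculation nevertheless assumes five controls per patient, all with a score, when the only described route to a score is through DMW itself. The 534 people it needs with scores exceed both the recruitment minimum and the reported enrolment.

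The kind of control matters too. While the offer is open to everyone, DMW users without the intervention are those who chose not to take it. Once a cap is reached, further controls enrol later than the treated, in a study that runs through the pandemic. An 80% power figure suggests a firm controlled comparison, which the described data flow may not deliver. With the objective worded two ways, it is also unclear whether a between-group or a within-person result will be the headline.

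**Working it through.** **Inputs from the protocol article:** SD 0.92; difference 0.3; 5% significance (sidedness not stated; two-sided reproduces the figure); 89 patients and 445 controls; 90% providing data; minimum DMW enrolment 288; 316 enrolled.

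**1. Reproduce the stated figure.** With k = 5 controls per patient,

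n = (1.960 + 0.842)² × 0.92² × (1 + 1/5) / 0.3² = 88.6, rounded up to 89; controls 5 × 89 = 445.

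Allowing for loss, 89 / 0.9 = 98.9, so 99. The power of 89 v 445 by the noncentral t is 80.0%. The stated numbers are correct for their inputs.

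**2. People needed with a score.** 89 + 445 = 534. If controls also lose 10%, 445 / 0.9 = 494.4, so 495, and total enrolment is 99 + 495 = 594. Stated enrolment is 288 (minimum) or 316 (interim count).

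**3. Most controls available within DMW.** Suppose 99 people take the intervention and everyone else becomes a control with a score:

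- 288 − 99 = 189
- 316 − 99 = 217

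With 10% loss: 189 × 0.9 ≈ 170 and 217 × 0.9 ≈ 195.

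If only 15-50% of the 217 give a score (an assumption, since the document gives no rate): 0.15 × 217 ≈ 33 and 0.50 × 217 ≈ 108.

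**4. Power at those numbers.** SE = 0.92 × √(1/n₁ + 1/n₂); noncentrality = 0.3 / SE; two-sided 5% t test with n₁ + n₂ − 2 degrees of freedom.

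| Patients v controls | SE | Noncentrality | Power |
|---|---|---|---|
| 89 v 445 (as stated) | 0.107 | 2.81 | 80.0% |
| 89 v 217 | 0.116 | 2.59 | 73.3% |
| 89 v 189 | 0.118 | 2.54 | 71.5% |
| 89 v 195 (10% loss) | 0.118 | 2.55 | 71.9% |
| 89 v 170 (10% loss) | 0.120 | 2.49 | 70.0% |
| 89 v 108 (assumed) | 0.132 | 2.28 | 62.0% |
| 89 v 33 (assumed) | 0.188 | 1.60 | 35.5% |

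The difference detectable with 80% power, (1.960 + 0.842) × SE, is about 0.33 with 189 controls and 0.32 with 217, against the planned 0.30.

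**5. Sensitivity to uptake.** Step 3 fixes uptake at the planned 99. If more people took the intervention, the split would be more even. With every enrolee giving a score, 144 v 144 has 78.7% power and 158 v 158 has 82.4%. With about 10% loss in both groups, 130 v 130 has 74.5% and 142 v 142 has 78.2%. Power thus depends on uptake and score completion, and the protocol article gives no expected value for uptake.

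**6. Passages that do not agree.** The cap is 600 people offered in one section and 1000 completions in another; both exceed 288 and 316. The distress objective is within-person only in Textbox 1, but the controlled comparison is primary in Outcomes and is the one powered. Comparison Group takes comparators from NHS Digital, which supplies no score, while Enrollment and Informed Consent takes them from assessment completers within DMW.

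**The case against.** **Enrolment is not capped at 288 or 316.** The first is a minimum taken from the HbA1c evaluation, and the second is an interim count with a recruitment extension granted. DMW is to be offered to 140,000 people, and a further 278 tried to register but lacked GP permissions; 316 + 278 = 594, the total in step 2. This stands. A reader might infer that 445 controls are impossible, but the document shows only that they are unsupported.

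**Controls can exist before the cap.** A reader might infer that the control group forms only after 600 or 1000 people have had the intervention. The text does not say so: controls are defined by not receiving an optional intervention, so decliners qualify from the start, and they are concurrent. This stands. Their weakness is self-selection, which Comparison Group accepts openly for all the interventions.

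**A control data route through DMW is stated.** The MyCognition data section says that participant and control data come from MyCognition via DMW as well as from other sources. True, but distress scores are listed there under participant data, and nothing says that controls complete the questionnaire.

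**Baseline adjustment could recover the loss.** If baseline and follow-up scores correlate at 0.5 (assumed), the residual SD is 0.92 × √0.75 = 0.797, and 89 v 170 or 89 v 195 gives about 82% or 83%. This is fair and is a reason to plan the adjustment, but it needs a baseline score in controls and cannot help with controls who have no score.

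**Shortfall is anticipated.** The sample size section promises due consideration in interpretation if numbers are not reached. That does not supply a missing source for the outcome. The HbA1c comparisons are not affected by this point.

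**Conclusion.** The point holds in a limited form. The calculation is correct, but its control number is not supported by the data sources or the enrolment that the protocol article states. At 288 or 316 enrolees with 99 taking the intervention, power is at most about 71-73% unadjusted, or 70-72% if controls lose 10% as patients are assumed to. If only 33-108 controls give a score, it is about 36-62%; that range rests on an assumed 15-50% completion rate. Greater uptake or greater enrolment would raise these figures.

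The loss of power at the upper bound is modest. The larger problem is that three things are not settled consistently: where a control's distress score comes from, who the controls are, and whether the primary result is between-group or within-person. The two caps also conflict. The document does not show that the comparison must fail or that no concurrent control can exist.

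**What to change.** 1. Replace the 89/445 statement with power for the number of within-DMW controls that can realistically be reached, giving the assumed uptake and score completion.
2. State that these controls complete the distress questionnaire at the same 3-monthly assessments as the treated.
3. Adjust the comparison for baseline distress score.
4. Reconcile the two statements of the cap (number, and whether it counts offers or completions), and align Textbox 1, Design, Comparison Group, Outcomes and the sample size section on one control group and one primary estimand.
5. State that if concurrent controls with scores are too few, the result will be reported as an uncontrolled within-person change.

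Items 1 and 3 to 5 cost wording only. Item 2 is also wording if controls already receive the questionnaire; otherwise it adds a web form for existing platform users.

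Allocating the MyCognition offer at random or by alternation would give concurrent controls not chosen by themselves, but it is an optional design change and not part of this fix. People already enrolled have had access to the offer, and a comparison by offer is diluted by non-uptake: with 129 v 130 analysed and 50% uptake (assumed), the difference falls to 0.15 and power to about 26%, or 33% with baseline adjustment at r = 0.5.

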### Economic Evaluation

#### Short-term Health Benefits and Consequences to Costs

In the short term, economic evaluation will focus on the cost-effectiveness of DMW measured over the intervention period (up to December 2020). Data on changes in outcomes from the quantitative evaluation, such as HbA_1c_ levels, will be compared against costs across population groups. Relevant costs will be direct NHS costs assessed from intervention-related costs and changes in routine health care use, as assessed from rates of primary care consultations and hospital attendance during the observation period. The unit costs of delivering traditional face-to-face behavior change interventions and psychological interventions are available in GM, enabling meaningful cost comparisons. Further unit costs will be sources of NHS reference costs and the unit costs of health and social care.

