DMW has evolved based on the evidence base generated from the Scottish pilot and now incorporates an app to be used with mobile devices, which includes tailored *push* decision support, including health warnings and reminders to patients and clinicians. It is this enhanced version of DMW that, as part of the GM Diabetes My Way project, will be offered to all patients with T2D in GM from August 2019 to March 2022. DMW in GM is a collaborative led by the Greater Manchester and Eastern Cheshire Strategic Clinical Networks. Their aim is to provide a more comprehensive self-management and learning offer than is currently available to people with T2D in GM by delivering an enhanced version of DMW across the region. An additional aim is to improve the uptake of the system across all patient groups.

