**Diabetes My Way–related objectives**
To assess intervention-related changes in hemoglobin A_1c_ (HbA_1c_) levels, systolic blood pressure, cholesterol, smoking, and body weight or BMI (compared with controls and within-person changes).To assess patient uptake (proportion offered intervention who take it up), engagement (time spent on the web and content viewed), user experience (usability, knowledge, and ability to self-manage), retention (proportion of people interacting with the intervention more than once), completion (proportion of people interacting with the intervention who use it within 2 months of the end date (March 31, 2022), and health care use (clinic and hospital attendance and medication use).To assess how Diabetes My Way (DMW) is integrated into care pathways in primary care.

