#### Duration of Data Access

The University of Manchester will request primary care data on study participants for the period April 1, 2016, to March 30, 2022, through DMW This will enable a 3-year assessment of *baseline* levels of risk factors such as HbA_1c_ and blood pressure before study commencement (July 2019), and up to the end of the intervention (March 31, 2022).

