In the presence of time series data, we will use an interrupted time series design for each outcome of interest, which takes into account the preintervention trends of the outcome as well as the information on controls and quantify the effect of the intervention on future outcome levels. If only 2 time points are available (eg, before and after the intervention), we will use a simple linear regression model with clustered errors or a paired 2-tailed *t* test to compare means in each outcome at the 2 time points.

For example, for the main outcome, change in HbA_1c_ levels, we will compare changes from baseline (defined as April 1, 2016, to July 1, 2019) during the intervention period (July 1, 2019, to March 31, 2022) in matched participants and controls after adjusting for clinically significant differences in baseline weight, blood pressure, cholesterol, creatinine, cardiovascular disease, and smoking.

If the numbers of cases and controls are large, we will explore effect heterogeneity in subgroup analyses (as separate models or using interaction terms in the main models described above) by ethnicity, age groups, socioeconomic deprivation quintile, cognitive function (assessed by MyCognition), and level of engagement with digital interventions.

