## Results

As of May 10, 2021, a total of 316 participants have been recruited for the quantitative study and have successfully enrolled. A total of 278 participants attempted to register but did not have appropriate permissions set by the GPs to gain access to their data. A total of 10 participants have been recruited for the qualitative study (7 practitioners and 3 patients). An extension to recruitment has been granted for the quantitative element of the research, and analysis should be complete by June 2022. Recruitment and analysis for the qualitative study should be complete by June 2021.

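### The short-term cost-effectiveness analysis ends the intervention period at December 2020, whereas the rest of the protocol, including the evaluation supplying its effects, ends it in March 2022

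*Protocol article*

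**What the plan says.** The Economic Evaluation, under Short-term Health Benefits and Consequences to Costs, says that "economic evaluation will focus on the cost-effectiveness of DMW measured over the intervention period (up to December 2020"). The next sentence gives the source of the effects: "Data on changes in outcomes from the quantitative evaluation", with HbA1c as the example, are to be compared with costs. Costs are intervention-related costs plus changes in routine health care use. The use is counted over an observation period for which the section gives no dates.

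Four other places date the end of the intervention:

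- Analysis, Overview, for the main HbA1c comparison: "during the intervention period (July 1, 2019, to March 31, 2022) in matched participants and controls".
- Duration of Data Access: "up to the end of the intervention (March 31, 2022").
- Background, on the roll-out: DMW "will be offered to all patients with T2D in GM from August 2019 to March 2022".
- Textbox 1, in the DMW objective that defines completion: people who "use it within 2 months of the end date (March 31, 2022").

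The Results section reports 316 people enrolled as of May 10, 2021 and adds: "An extension to recruitment has been granted for the quantitative element of the research".

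**The concern.** One term, the intervention period, has two end dates, and the two sections that use it feed the same calculation. A cost-effectiveness figure is interpretable only if costs and effects come from the same people over the same time. Here the effects come from an evaluation that runs to March 31, 2022, while the sentence defining the cost-effectiveness analysis stops at December 2020. An analyst following the economic section literally would have to choose which quantities to cut, and the choice changes both the time covered and the people included.

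Cost-effectiveness is one of the overarching objectives in the Abstract and the first secondary aim under Aims and Objectives, so the section serves a named purpose. The primary HbA1c analysis is not affected.

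**Working it through.** The protocol gives no figure of its own to reproduce. The check compares the dates.

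**Inputs**

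- Start of the intervention period: July 1, 2019 (Analysis, Overview). The Background has DMW offered from August 2019, used below as a sensitivity check.
- End for the economic evaluation: December 2020, taken as December 31, 2020.
- End for the outcomes: March 31, 2022 (Analysis, Overview; Duration of Data Access; Textbox 1).

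**Length of each window**

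- Economic: July 1, 2019 to December 31, 2020 = 549 days, or 18 calendar months.
- Outcomes: July 1, 2019 to March 31, 2022 = 1,004 days, or 33 calendar months.
- Share covered: 18/33 = 55% (549/1,004 = 0.547).
- Omitted: 1,004 − 549 = 455 days, or 33 − 18 = 15 calendar months.
- With an August 1, 2019 start: 518/973 = 0.532, about 53%.

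**Who falls outside.** Anyone enrolled from January 2021 has zero time in the economic window but counts in the effectiveness analysis. The enrolment figure of 316 is dated May 10, 2021, which is 130 days after December 31, 2020, and recruitment was being extended. The 316 are not split by enrolment date. The documents therefore bound the number affected only trivially: between 0 and 316 of those already enrolled, plus anyone who joined later.

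**What the wording permits**

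1. *Costs stop at December 2020 and effects run to March 2022.* Costs and effects then cover different periods and, for later enrolees, different people.
2. *Costs and effects both stop at December 2020.* They match each other, but the effect is no longer the one from the main evaluation, and about 15 months of requested data are unused.
3. *December 2020 is an outdated date and both run to March 2022.* There is no mismatch, but the sentence is wrong as it stands.

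No reading leaves the section consistent with the rest of the protocol without a change of text.

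**Data available.** The sections on data items and on NHS Digital data list medication, diabetes clinic attendance in primary care and hospital visits, for participants and controls, to March 30 or 31, 2022. The one-day difference between those dates is immaterial here.

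**The case against.** The strongest reply is that the section opens by confining itself to the short term, so an earlier cut-off may be deliberate. That does not hold. The phrase sets within-study results against the modelled long-term results in the section that follows. The December 2020 date explains the intervention period itself, and no separate shorter horizon is stated or justified.

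A second reply is that the text does not say costs alone are cut. This stands. The date is attached to cost-effectiveness as a whole, and resource use is tied to an undated observation period that could run to March 2022. A mismatch between costs and effects is therefore one reading, not something the protocol states.

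Three stronger inferences are tempting, and the documents do not support them:

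- *Later enrolees have no cost data.* Health care use is requested to March 2022 for participants and controls. At most, those data would go unused in this one analysis.
- *The long-term model receives wrong inputs.* The long-term section works through changes in risk-factor levels and names no input cut at December 2020.
- *The retained months are those most distorted by the pandemic.* The COVID-19 note gives no dates for the disruption and says limited access may continue for many months.

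**Conclusion.** The contradiction in dates is real and should be corrected. Taken literally, the short-term economic window is about 18 of 33 calendar months (55%, or 53% from an August 2019 start) and gives no time to anyone enrolled from January 2021. The consequence depends on the reading: costs and effects from different periods and people if only costs are cut, or about 15 months of requested data unused if both are cut.

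This assumes that December 2020 means the end of that month and that the economic window starts with the outcome window, since the economic section gives no start date. The percentages describe calendar time. Enrolment was staggered and its timing is not reported, so they do not give the share of people or person-time lost, and no change in incremental cost can be calculated. That December 2020 is left over from before the recruitment extension is plausible, but it is an inference.

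**What to change.** In the short-term economic section, replace December 2020 with March 31, 2022. Give the observation period for resource use the same start and end dates as the outcome analysis, and state that costs and effects are taken from the same participants and matched controls over the same window.

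If a shorter economic horizon is intended, say so, give the reason, and cut the outcomes used in that analysis at the same date. It should then be stated that people enrolled afterwards do not contribute to it.

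The first option costs one corrected date and a sentence or two, because health care use is already requested to March 2022. The second also needs effect estimates re-run to the earlier date. A fixed follow-up length per person, such as 12 months, is a separate design choice and is not needed here. Anyone enrolled after March 2021 could not complete 12 months by March 31, 2022.
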